### Intervention

#### Development

The C2M intervention has been developed from a participatory research approach, with academics working alongside other stakeholders [37]. The development process of the C2M intervention includes a systematic review [27], two qualitative studies, including employers and employees [38] and a Delphi study with experts on occupational health and PA promotion [31]. Moreover, C2M followed the new Medical Research Council (MRC) framework on the development of complex interventions to improve health [39, 40]. Firstly, a systematic review and meta-analysis was conducted to examine the effectiveness of digital workplace interventions to reduce time spent in SB in office workers [27]. Nineteen randomised controlled trials were included in the systematic review, eleven of which were used in the meta-analysis. A wide range of digital elements and working strategies were described among the included studies. Delivery of information and educational materials through text messages, e-newsletters, websites or videos for increasing knowledge and awareness were the most common digital workplace strategy. Scheduled prompts to break SB or participate in PA delivered via computer screens and mobile phone applications were the second most common digital workplace strategy. The results of the study indicated that multicomponent digital interventions, including elements at organisational, environmental, and at the individual level are effective to reduce workplace SB, presenting a reduction of 29.9 min/8 h workday [27].

In addition, the perspectives of managers (*n* = 20) and employees (*n* = 51) across three countries, namely Ireland, Spain and The Netherlands were gathered through semi-structured interviews, allowing for an in-depth perspective on a multinational basis and was guided by the COM-B model [38, 41]. The interviews were conducted online, and a reflexive thematic analysis approach was adopted to analyse the data and develop themes and sub-themes. Both employees and managers highlighted the need for a top-down approach to the intervention, whereby organisational support was provided to employees, which would create the freedom and opportunities to reduce SB and engage in PA during work. Employees highlighted the need for a flexible intervention, which catered for the wide range of fitness levels and interest that exist within an organisation, with the provision of a range of time-efficient exercises that employees can chose from identified as a viable approach to reduce and break up SB. The need for a multicomponent intervention, which incorporates an educational element on the health benefits of SB, was also highlighted by both employees and managers. Finally, managers highlighted the possibility of leveraging infrastructure put in place during the Covid-19 pandemic, such as online educational provision or the use of digital platforms such as mobile phones for supportive messaging, to further support those working from home.

Lastly, a modified Delphi study to reach experts’ consensus on the most feasible strategies and the most usable digital elements as a delivery method to reduce SB in home-office context was performed [31]. Work strategies and digital elements, which were selected from a scoping review of workplace PA strategies across Europe [42], the previous systematic review [27] and the needs assessment [38], were classified according to the Behaviour Change Wheel (BCW) and the Behavioural Intervention Technology (BIT) elements. Eighteen feasible work strategies were identified, with feedback on activity progress and goal achievement, creation of an action plan or giving information to increase awareness and knowledge being the highest ranked. An additional 16 digital elements were identified as useful for inclusion within the intervention, including the use of wrist-based activity trackers, app interface in mobile phones or gamification features.

To refine and improve the C2M intervention, we conducted a single-group pilot study over a one-week period. Twenty-one participants across the four countries involved in the C2M project participated in the study. The usage, usability, acceptability, perceived usefulness, and satisfaction of the C2M intervention were assessed through four 5-point Likert scales and three open ended questions. Participants used the C2M App for an average of 4 days for 8 h each day. The App was considered as acceptable, and easy to use. Additionally, the activity tracker was perceived to improve the App information. Participants perceived the contents of the programme as “quite a bit useful”, with the exception of cooperative challenges, considered not useful/not useless. Participants were satisfied with the programme, with the awareness about their own activity patterns being the most liked item, while connection issues between the activity tracker and the application were the largest issues identified. Consequently, post-test modifications were performed to address the reported major issues.

Figure 2 provides the logic model of the C2M intervention development. For each element of the intervention, the intervention type was identified according to the intervention functions from the BCW [43], the Behaviour Change Techniques (BCT) using the BCT’s Taxonomy v1 [44], and the digital elements applying the BIT classification [32].

**Fig. 2 Fig2:**
[figure not shown]
Logic model of the Click2Move intervention development

#### Components

The C2M intervention is a multicomponent program addressing multiple levels (i.e. the environmental, organisational and individual level) aiming to reduce sitting time during working hours. The intervention includes a mobile phone application (C2M App) available in five European languages: English, Spanish, Catalan, Dutch, and Slovenian, alongside an activity tracker (Fig. 3), comprising environmental, organisational, and individual implementation levels.

**Fig. 3 Fig3:**
[figure not shown]
The wrist-worn activity tracker initialized with the C2M App

The C2M App is compatible with both Android and iOS platforms and connects to an activity tracker via Bluetooth. The App receives accelerometer data and interprets it using JS libraries within React Native. Furthermore, it communicates through an API hosted on a server within the C2M host institution. The activity tracker is a waterproof wristband (1810G Monitor Smart Band, Joint Chinese Ltd., Guangdong, CHN; dimensions = 42*19*11.2 mm main body; 204.6*16.8 mm). It operates using a durable 110mAh lithium battery with a built-in USB charger and is equipped with a triaxial accelerometer sensor.

The *environmental level* is comprised of a person’s situation or environment that encourages them to break their sitting time at work [45]. Activity tracker and App provision, sedentary reminders, cooperative challenges, and social chat are the environmental elements that will be part of this level.

The activity tracker, apart from tracking activities, provides sedentary reminders through vibrations and a message displayed on the screen of the wristband. Every uninterrupted hour without moving from the chair will result in the alert/message being displayed. After receiving the sedentary reminder on the activity tracker (Fig. 4a), the user will enter the C2M App, where a message will appear inviting them to perform a suggested active break (or strategy) (Fig. 4b). The user will be able to accept the strategy (by agreeing to complete the strategy) or to skip it.

**Fig. 4 Fig4:**
[figure not shown]
**a**. Activity tracker sedentary remainder (image provided and adapted from Joint Chinese Ltd.)**b**. C2M app sedentary reminder

The C2M App will offer monthly cooperative challenges for all participating company employees on the “Challenges” page. Examples include reaching a step goal or limiting the number of sedentary reminders received. Each challenge includes a title, description, and duration, as well as collective and individual achievement tracking. Each challenge will include a “social chat” where users will be able to share their experiences with other employees (Fig. 5).

**Fig. 5 Fig5:**
[figure not shown]
Challenges and social chat

The *organisational level* includes social pressure, social norms, social support, policies, rules, regulations, interaction with colleagues, and modelling that can cause individuals to change their behaviour [45, 46]. The C2M programme follows a top-down approach, involving the company in the dissemination, recruitment, and implementation phases. In addition, a monthly feedback survey and motivational messages are also strategies to be implemented at this level to provide further opportunities to break up prolonged SB.

Specific company actions include (a) internally communicating the C2M initiative (e.g., through face-to-face or virtual presentations), (b) sending invitation emails for participation to employees, and (c) leading by example in the social chat of the App to promote engagement (i.e., managers demonstrating to employees the active breaks they are engaging in). Additionally, the C2M program will feature a permanent suggestion box on the “Profile” page of the App (Fig. 6) and monthly short surveys to gather participant feedback. Participants will also receive motivational messages related to challenge achievements and for avoiding prolonged periods of sedentary time (Fig. 7).

**Fig. 6 Fig6:**
[figure not shown]
Suggestion box

**Fig. 7 Fig7:**
[figure not shown]
Motivational message

The *individual level* considers elements to enhance the individual’s adoption and maintenance of the behaviour (e.g., knowledge, education) [47], such as self-monitoring and feedback provision, active break strategies together with demonstrative videos and educational material.

Users will self-monitor their working hours activity through the activity tracker and real-time feedback will be displayed on the “Home” of the C2M App. This includes metrics such as step count, time spent sedentary, status of sedentary reminders (accepted or declined), and completion status of additional strategies chosen by users without reminders. This data will also be visualized in a time continuous loop with each segment differentiated by color: green for activity time, yellow for sedentary time with bouts of less than one, and red for longer periods of sedentary time (> 1 hour). Furthermore, users can access their activity history through the “History” page (Fig. 8).

**Fig. 8 Fig8:**
[figure not shown]
Self-monitoring feature

A list of general strategies (e.g., walk during the meetings) and active break strategies covering the following wide range of exercise types (i.e. walking, stretching, strengthening, mobility and stability) will be available on the “Strategies” page of the App (Fig. 9). Participants will be able to *like* them, and the more popular strategies will appear as preferred exercises. Each strategy will include a title, an image, a description, and a video demonstration on how to implement/complete them. Additionally, the active break strategies will be randomly suggested on the sedentary reminders message.

**Fig. 9 Fig9:**
[figure not shown]
List of strategies

Finally, participants will receive monthly emails with educational material (i.e. infographics) with the aim of increasing participants’ knowledge and awareness for breaking prolonged periods of uninterrupted sedentary time. Moreover, in the description of each strategy, the benefits of implementing that strategy will be provided.

#### Intervention arm

Participants from the intervention group will be invited to a face-to-face meeting to provide them with an activity tracker, and to provide a printed tutorial outlining how the App should be used. They will be asked to download the C2M App on their own mobile phone and wear the activity tracker during working hours for one year. Before the meeting, participants will be registered from the C2M App back office by the representative researchers in each country. During the meeting, the researchers will explain and demonstrate (a) how to initialise the App through the App wizard that will guide the user through the activity tracker synchronization, setting their work hours (Fig. 10), and (b) the wide range of App functionalities.

**Fig. 10 Fig10:**
[figure not shown]
Synchronization and working hours settings

#### Control arm

Control group participants will not receive any device, nor will they have to download the mobile phone App. They will be asked to maintain they regular behaviours at work during the study period.

### Data collection

Data will be collected at four time points for both the intervention and control group participants: at baseline (T0), short term (after 3 months, T1), medium-term (6 months, T2), and long-term (12 months, T3). Measurements consist of online self-report questionnaires, an activPAL^3TM^ monitor (PAL Technologies Ltd., Glasgow, UK) and focus groups. See schedule of the enrolment, intervention, and assessments in Table 1.

The online questionnaires will be delivered through the REDCap (Research Electronic Data Capture) platform via email prior to the first appointment. The researcher will ensure that participants have completed the questionnaires online; otherwise, they will be asked to complete the questionnaires during the appointment. One week after sending the email, trained researchers will provide participants with the activPAL^3TM^ device and the diary log, along with an activPAL^3TM^ video and a hard copy tutorial.

#### Socio-demographic and home-environment measures

At baseline, participants will be asked for their age, gender, anthropometrical measures, educational level, general working conditions, home-working environment, mode of commute to and from work (on office working days), and behavioural habits (i.e. sleep conditions, and tabaco and alcohol consumption).

#### PA and SB outcomes

The activPAL^3TM^ will be used to measure and quantify the occupational and leisure PA and SB of employees, including sitting, standing, and stepping time, number and duration of sedentary bouts, sedentary to non-sedentary transitions, light Intensity PA and MVPA. The activPAL device is a valid measure to quantify body posture and activity patterns during free-living conditions in a range of populations, including healthy adults [48]. The device will be attached to the midline of the anterior aspect of the participants’ right thigh using a flexible nitrile sleeve and a transparent film (10 × 10 cm of hypoallergenic Tegaderm™ Foam Adhesive Dressing). Participants will wear the activPAL^3TM^ for 7 consecutive days, 24 h/day. Additional dressings and instructions on how to reattach the device will also be provided. Furthermore, participants will be asked to record their daily wake time, bedtime, working hours, working location (office vs. home-office), the mode of commute, PA context and any monitor removal time through the activPAL^3TM^ diary. Data will be processed using activPAL^3TM^ Professional Software™ (version 7.2.32), Microsoft Excel 2010 (Redmond, WA, USA), and MATLAB v8.4 (MathWorks^®^, Natick, MA, USA), following previously published procedure for data reduction and cleaning [49, 50, 51].

PA will also be self-reported using the Global Physical Activity Questionnaire (GPAQ), a valid and reproducible questionnaire [52]. The GPAQ questionnaire contains fifteen questions regarding PA in three domains (occupational PA, PA for transportation to and from places and PA during recreational activities). Self-reported SB will be measured through the Workforce Sitting Questionnaire (WSQ), which has previously been demonstrated to have excellent test-retest reliability and acceptable validity [53]. Five items will assess sitting time on working and non-working days in a range of domains (a) traveling, (b) at work, (c) watching television, (d) using a computer at home (outside of work), and (e) other leisure activities (but not including watching television or using computer).

#### Health-related outcomes

Health-related outcome will be operationalised by musculoskeletal symptomatology and pain intensity. Musculoskeletal symptomatology will be measured through the Standardised Nordic Questionnaire (SNQ), while pain intensity will be measured using the 11-point Numeric Rating Scale (NRS). The SNQ is an internationally self-administered questionnaire, designed for the exploration and identification of musculoskeletal symptoms, primarily in the working population. The general questionnaire consists of 8 questions with dichotomous and Likert scale (4 to 5 levels of response) responses. In all questions, it is necessary to specify for each of the 8 body parts included: neck, shoulders (differentiating between the right and left), back (differentiating between the upper and lower part), elbow-forearm (differentiating between the right and left), hand-wrist (differentiating between the right and left), hip/thigh, knees, and ankles/feet. The questions refer to the presence of discomfort, both in the last 12 months and in the last 7 days; the duration of discomfort and each episode of pain in the last 12 months; the duration of temporary disability derived from discomfort in the last 12 months; the need for treatment for the discomfort presented in the last 12 months; the intensity of discomfort present in the last 7 days; and finally, the cause of discomfort in the last 7 days. The SNQ has been demonstrated as a valid, reliable and feasible tool that enables the identification of musculoskeletal problems among different anatomical areas in epidemiological and ergonomic studies [54]. The NRS consist of a numeric version of the visual analogue scale, with a horizontal line labelled from zero to ten, with zero being an example of someone with no pain and ten being the worst pain possible. The NRS has shown high sensitivity, reliability, and validity to identify pain intensity [55].

#### Work-related outcomes

Presenteeism and absenteeism will be assessed with seven questions from the Health and Work Performance Questionnaire (HPQ) [56]. The HPQ demonstrated good validity [57], while it has also demonstrated strong reliability and sensitivity to change [56]. Four open questions on the number of days and hours participants work the past 7 days, the number of hours the employer expects employees to work in the past 7 days or in a typical 7-day week, and the number of hours participants work in the past 4 weeks will be used to score the absolute presenteeism. The number of entire or partial days missed in the past 4 weeks for mental or physical health or for other reasons (e.g., vacations) will be used to score the relative absenteeism. A high score indicates a higher amount of absenteeism. These questions are followed by two questions that ask employers to rate working in their job on a 0–10 scale of work performance (worst to best) and rank themselves over the past 4 weeks. Absolute presenteeism will be calculated as the difference between the score for one participant the past 4 weeks and the score for the average worker in the same job. In this case, a higher score indicates lower amount of lost performance. A relative presenteeism score can be computed as the ratio of individual versus other scores.

The Need for Recovery scale has demonstrated good and consistent validity to measure occupational fatigue [58]. Additionally, the Need for Recovery scale has shown favourable test-retest reliability and sensitivity to detect change [59]. The Need for Recovery comprises of eleven items with yes/no responses. A score is calculated by adding all the scores of the individual items and transforming these into a scale from 0 to 100. Higher scores indicate a higher need for recovery after work.

Job satisfaction will be measured using a single-item 5-point Likert scale [60], where 1 is extremely dissatisfied and 5 extremely satisfied. The standard satisfaction scale ranging from 1 to 5 will be converted into 0 to 100 scales using the formula: AdjSS = 100 x [stsSS-1] / [5 − 1], where adjSS and stdSS will be “adjusted satisfaction score” and “standard satisfaction score”, respectively. With the new scoring method, job satisfaction falls into 5 categories: “extremely dissatisfied” ([adjSS: 10–29], “dissatisfied” [30–49], “generally satisfied or not” [50–59], “satisfied” [70–89], and “extremely satisfied” [90–100] [61].

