**Methods:**

A two-arm cluster randomised controlled trial will be undertaken among hybrid office employees. In total, 200 employees will be recruited across four companies across Europe (The Netherlands, Spain, Ireland, and Slovenia). Participants within each company will be randomly allocated to the intervention or control group at the unit/cluster level. The intervention group will receive the novel multicomponent Click2Move intervention (including environmental, organisational, and individual strategies) for 12 months, and the control groups will maintain their usual work practices. The primary outcome will be occupational sedentary time measured via activPAL^3TM^ at baseline and at 3, 6 and 12 months follow-up. Secondary outcomes will include device-based (activPAL^3TM^) and self-reported (Global Physical Activity Questionnaire and Workforce Sitting Questionnaire) physical activity and sedentary behaviour; self-reported musculoskeletal disorders (Standardised Nordic Questionnaire) and pain (Numeric Rating Scale); self-reported presenteeism and absenteeism (Health and Work Performance Questionnaire), job satisfaction (Need for Recovery scale) and fatigue (single-item 5-point Likert scale). Focus groups will be conducted with employees post-intervention. Linear mixed models, accounting for covariates, will be employed to determine the effects of the intervention. Additionally, we will perform a full process evaluation analysis.

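### The job-satisfaction conversion and its category bands do not fit each other, so any report by category would be wrong for responses 1 and 2

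*Protocol article*

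**What the plan says.** Under Work-related outcomes, the protocol article measures job satisfaction with a single five-point item, "where 1 is extremely dissatisfied and 5 extremely satisfied". Only these two end points are labelled.

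It then rescales the item: "The standard satisfaction scale ranging from 1 to 5 will be converted into 0 to 100 scales using the formula", the formula being 100 × (score − 1)/(5 − 1).

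Finally it groups the rescaled score: "With the new scoring method, job satisfaction falls into 5 categories". The five bands are:

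- extremely dissatisfied, 10–29
- dissatisfied, 30–49
- a middle category, 50–59
- satisfied, 70–89
- extremely satisfied, 90–100

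The same section assigns the Need for Recovery scale to occupational fatigue. The abstract pairs the instruments the other way round: "job satisfaction (Need for Recovery scale) and fatigue (single-item 5-point Likert scale".

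The Data analysis section plans linear mixed models for the intervention effects, and effect sizes formed from the difference in group means. It does not mention the satisfaction bands.

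**The concern.** A five-point item put through a linear formula has only five possible results. Five bands with five ordered labels ought to receive one result each, in order. The bottom band starts at 10, whereas the formula starts at 0, so the lowest response appears to have nowhere to go and the next one appears to take its place.

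What is at stake is any table or figure that shows job satisfaction by category. Followed literally, the rule would leave the least satisfied workers unclassified, put those who answered 2 under the most extreme negative label, and always show an empty dissatisfied row. A worker who moved from 1 to 2 would pass from unclassified to extremely dissatisfied, so an improvement would look like a new extreme case.

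**Working it through.** **Inputs**, all from Work-related outcomes: raw responses 1, 2, 3, 4, 5; the conversion 100 × (score − 1)/4; the five bands listed above.

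**Step 1. Check the formula against its stated range.** The lowest response gives 100 × (1 − 1)/4 = 0 and the highest gives 100 × (5 − 1)/4 = 100. The formula delivers the 0 to 100 range that the text promises, so it is coherent in itself.

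**Step 2. Convert each response and look it up in the bands.**

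| Response | Conversion | Result | Band it falls in |
|---|---|---|---|
| 1 | 100 × 0/4 | 0 | none |
| 2 | 100 × 1/4 | 25 | extremely dissatisfied (10–29) |
| 3 | 100 × 2/4 | 50 | middle (50–59) |
| 4 | 100 × 3/4 | 75 | satisfied (70–89) |
| 5 | 100 × 4/4 | 100 | extremely satisfied (90–100) |

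The stated five categories are not reproduced. Four can be filled, 30–49 cannot, and one response is left over.

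**Step 3. Look for uncovered values.** The bands omit 0–9 and 60–69. The first gap matters because response 1 lands in it. The second does not, because no response converts to a value there.

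**Step 4. See whether another simple rescaling fits the bands.**

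- 100 × score/5 gives 20, 40, 60, 80, 100. Every result finds its band in order except 60, which falls in the 60–69 gap.
- 100 × (score − 0.5)/5 gives 10, 30, 50, 70, 90. All five fit in order, but the results do not span 0 to 100.

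Neither is the formula in the protocol. They show only that the bands could suit some other conversion, not which one was intended.

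**Step 5. Check the effect on the planned analysis.** The conversion can be written as 25 × score − 25. Differences in means and standard deviations are both multiplied by 25, so their ratio is unchanged. A linear model of the 0–100 score gives the same test results as one of the raw score, and neither uses the bands.

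**The case against.** The strongest reply is that nothing planned depends on the bands. Data analysis names linear mixed models and mean-based effect sizes, both of which use a numeric score. It mentions frequencies for describing the main variables at baseline and for the process-evaluation questionnaires, but does not refer to these categories. The raw 1–5 response is collected, so correct labels can be assigned at any time. All of this stands, and it limits the point to categorical reporting.

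A reader might infer more in four respects, and the documents do not support it.

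- **That the analysis of this secondary outcome is invalid, or that dissatisfied workers drop out of it.** The bands are not an input to any analysis described, and the numeric score keeps every response.
- **That the protocol itself labels response 2 dissatisfied.** It labels only 1 and 5. Reading 2 as dissatisfied is natural with five ordered labels on a five-point item, but it is an inference. The failure of response 1 and the empty band need no such inference.
- **That the 60–69 gap is a further scoring error.** It may be a slip in the upper limit of the middle band. It affects no response, and closing it would not repair responses 1 and 2.
- **That two of five options means two-fifths of participants.** The documents give no expected distribution of responses, so the number of people affected is unknown.

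One could also suppose that the bands are meant for group averages rather than individual answers. The text does not say so. On that reading the 60–69 gap would begin to matter: a mean response of 3.5 converts to 100 × 2.5/4 = 62.5, which has no band.

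On the abstract, the Methods text is unambiguous and gives scoring for each instrument. The swap is therefore an editorial slip and adds no weight to the scoring problem. Whether the registry record repeats it cannot be judged from the document at hand.

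**Conclusion.** The point holds as a contradiction within one section. The conversion and the bands cannot both be followed: response 1 is unclassified although the text defines it as extremely dissatisfied, response 2 takes that label instead, and the dissatisfied band stays empty. Responses 3, 4 and 5 are placed sensibly.

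The consequence is conditional and small. It arises only if job satisfaction is reported by category, and then only for those who answer 1 or 2. Analysis of the continuous 0–100 score, the primary outcome and the sample size are unaffected. The conclusion on response 1 rests only on the stated formula, anchors and bands. Calling response 2 misplaced rests in addition on the natural ordering of the five labels.

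**What to change.** Replace the bands with a one-to-one assignment of the five labels, in order, to the raw responses 1 to 5. This is the same as assigning them to 0, 25, 50, 75 and 100. Keep the 0–100 score as a linear rescaling for the numeric analysis. If the sponsor prefers to keep bands, formula and bands must be reconciled so that each response falls in exactly one category and every category can be reached.

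As a separate editorial correction, make the abstract agree with Work-related outcomes: the Need for Recovery scale for occupational fatigue, the single item for job satisfaction. This is worth doing because the two scores run in opposite directions: a higher Need for Recovery score is worse, whereas a higher satisfaction score is better.

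The cost is one sentence in the scoring text and one correction in the abstract. Nothing changes in data collection, sample size or the planned models.
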